## Abstract

**Background:**

Problematic use of digital technology among children, adolescents, and young adults is associated with adverse health, behavioural, interpersonal, social, academic and vocational outcomes. Most existing research focuses on treatment oriented interventions. Prevention focused interventions are limited. This is especially true for the low- and middle-income countries. There is a need for structured prevention approaches that involve youth, parents, and teachers.

**Objectives:**

This study aims to develop and validate a comprehensive package of prevention-focused interventions targeted at problematic use of digital technology among youth.

**Methods:**

The study will be conducted across six sites in India. It will use a sequential mixed-methods design. Literature review, stakeholder interviews, and expert consensus shall be used for intervention development. This will be guided by established frameworks for complex interventions. Validation will be carried out using a quasi-experimental pre–post design. Quantitative measures will assess changes in knowledge, skills, confidence, and decision-making, as well as feasibility and acceptability. Qualitative methods will be used to assess engagement, delivery quality, and contextual factors.

**Expected outcomes:**

The study will lead to a modular prevention-focused intervention package with evidence of feasibility and acceptability. Findings will inform future larger scale implementation and evaluations.

**Conclusion:**

This protocol outlines a structured approach to development of a prevention-focused intervention targeted at problematic digital technology use among youth. The focus on prevention, stakeholder involvement, and real-world settings supports relevance for public health practice and policy.

**Clinical trial registration:**

https://ctri.nic.in/Clinicaltrials/login.php, identifier CTRI2026/03/105278.

## Introduction

1

Digital technology is embedded in the daily lives of children, adolescents, and young adults. Digital devices and the internet related platforms support learning, work, leisure, and social contact. However, their poorly regulated use is linked to various adverse outcomes. These risks increase with early exposure and high daily screen time.

Problematic use of digital technology is a growing public health concern among the youth (article under review) (1–3). It has been associated with higher levels of depression, anxiety, stress, sleep disturbance, and reduced quality of life (4–9). Problematic use of digital technology is associated with higher levels of depression, anxiety, stress, sleep disturbance, and reduced quality of life (4–6). Patterns characterised by impaired control and continued use despite harm resemble behavioural addictions and may co-occur with substance use and suicidal risk (10, 11). Excessive engagement is also associated with reduced attention, academic decline, social withdrawal, and decreased offline interaction (12). Neuroimaging studies report altered brain connectivity related to self-regulation and reward processing among the youth. This increases their vulnerability to such problems (13).

Problematic use of digital technology refers to using technology in a pattern that leads to impaired control, increasing priority given to the behaviour, and continued engagement despite negative consequences. It may be associated with significant distress, dysfunction or both. This can manifest in the form of use of digital devices (online and offline) and the internet. It can occur in various contexts including use of the internet, smartphones, gaming, social media, gambling, shopping/buying, Over-The-Top (OTT) content watching, pornography watching, and excessive screen time. These are all potentially addictive behaviours. While many of these have not been listed as specified diagnostic categories, International Classification of Diseases (ICD-11) makes provision for listing these under the residual categories in the section on addictive behaviours (14).

Current responses to problematic digital technology use focus mainly on treatment after problems emerge (15). Preventive efforts are limited. Many programs address single behaviours or platforms and often exclude parents and teachers. Few interventions are designed for use across age groups or adapted to varied social and educational settings. Evidence from low- and middle-income countries (LMIC) remains limited (16).

In India, rapid growth in digital access has outpaced guidance on healthy use. Educational institutions and families often lack structured tools to support balanced digital technology use related behaviours. Differences in access, supervision, and digital skills add to this gap. Preventive interventions that are practical, theory-based, scalable, and suited to real-world educational and family settings are needed (14). However, such interventions remain limited in India (17, 18). International experience suggests that prevention of problematic digital technology use is most effective when education is combined with behaviour-change techniques and parental engagement. A recent rapid systematic review emphasized the importance of combining educational, behavioural, and environmental strategies (19). Systematic reviews of school-based prevention programmes recommend multi-component, theory-driven approaches. It is recommended that these programmes should incorporate skills training, self-regulation strategies, and stakeholder involvement (20). Programmes such as Be Internet Awesome and Stop and Play programme have been evaluated and found to be effective (21, 22).

This study protocol describes a structured process to develop and validate a comprehensive package of preventive interventions for problematic digital technology use among youth. The package targets youth, parents, and teachers through role-specific components. Development is guided by established frameworks for complex interventions and informed by literature review, stakeholder input, and expert consensus.

This study has been proposed as part of the Centre for Advanced Research on Addictive Behaviours (CAR-AB) (14). CAR-AB was established at All India Institute of Medical Sciences (AIIMS), New Delhi, in collaboration with leaders from health, public health, technology and education sectors and with the funding support from the Indian Council of Medical Research (ICMR). CAR-AB aims to establish a scientific, systematic, and sustainable framework for addressing addictive behaviours, and promoting digital and overall well-being among Indian youth. CAR-AB envisions promotion of safe digital technology use and enhanced digital well-being among Indian youth.

The current study will use a phased design. It will include intervention development, feasibility testing, and validation using mixed methods approach. This approach is intended to lead to systematic refinement and early assessment of feasibility, acceptability, and perceived impact.

### Objectives

1.1

The primary objective of the study is to develop and validate a comprehensive, prevention-focused package of interventions targeting problematic digital technology use among youth. The intervention also aims to address the associated stress, depression, anxiety and addiction. The target population includes the children, adolescents, and young adults. The intervention package will include components for youth, parents and teachers. The study also aims to assess the feasibility, acceptability, and perceived usefulness of the intervention package across diverse settings.

## Methods

2

### Study setting

2.1

Six sites will be included in the study. They represent different regions of India. These include New Delhi, Bhopal (Madhya Pradesh), Patna (Bihar), Puducherry, Rishikesh (Uttarakhand), and Shillong (Meghalaya).

### Study design

2.2

The study will be conducted in sequential phases. The first phase will focus on intervention development. This phase shall use an exploratory qualitative design. It shall also include a structured literature review. The second phase will involve validity testing of the developed intervention package using a quasi-experimental mixed-methods pre–post design. The participants will serve as their own controls. This design will allow assessment of feasibility, acceptability, and preliminary perceived impact, of the intervention (23, 24).

### Eligibility criteria

2.3

#### Inclusion criteria

2.3.1

##### For intervention development

2.3.1.1

The participants will include school and college students aged 12 years or older, parents, and teachers. In addition, mental health professionals, addiction experts, child and adolescent mental health experts, public health experts, and program or policy experts shall be included. Those providing informed consent or assent, as appropriate, shall be included in the study. Participants who decline consent will be excluded.

##### For validity testing

2.3.1.2

The participants will include school and college students aged 12 years or older, parents, and teachers. Those providing informed consent or assent, as appropriate, shall be included in the study. Participants who decline consent/assent will be excluded.

### Sample size

2.4

For intervention development: for focus group discussions (FGDs) and in-depth interviews (IDIs) recruitment will continue until data saturation is achieved for each stakeholder group. We anticipate conducting at least one FGD per stakeholder group per site, resulting in a minimum of 18 FGDs across six sites. Additional FGDs may be conducted if data saturation is not achieved. We anticipate conducting approximately 5–8 IDIs per stakeholder category across sites. Recruitment will continue until thematic saturation is achieved.

For feasibility testing: A minimum of five participants per group (i.e. youth, parents, and teachers) will be recruited from one school and one college at each site, resulting in a total sample of at least 30 participants. These participants will be different from the ones which were included in the sample for the development of the intervention package.

For validity testing: The minimum required sample size was calculated to detect a medium effect size of 0.5 with a two-sided alpha of 0.05 and a power of 95%. This resulted in a requirement of 53 participants per group. Accounting for an anticipated dropout rate of approximately 10%, at least 59 participants per group will be recruited. With three participant groups, the total planned sample size will be a minimum of 354.

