#### Feasibility assessment

2.6.4

Step 5 shall include testing and refining intervention on a small scale. The feasibility assessment of the intervention shall be carried out using a quasi-experimental, mixed-methods approach. Participants will be briefed in advance that this phase constitutes a feasibility and formative feedback assessment of a newly developed intervention package. Each group will be offered the interventions designed specifically for them (youth, parents, and teachers).Participants will evaluate each intervention on a Likert scale for clarity, perceived effectiveness, usefulness, and practicality. Additionally, a semi-structured questionnaire will gather qualitative feedback regarding their experiences, challenges, and suggested improvements. Students, parents and teachers will provide separate feedback on the individual interventions. The outcome of this step will be a set of feedback and recommendations regarding required changes to the package of prevention- focused interventions. The findings will be documented and shared with the expert panel for review. The experts will deliberate upon the findings and recommend the modifications for the intervention package.

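### The feasibility total of at least 30 does not follow from its own recruitment rule, which over six sites gives 90 or 180

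*Protocol article*

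**What the plan says.** The feasibility paragraph of Sample size (2.4) sets the rule and the total in one sentence. The rule opens with "A minimum of five participants per group (i.e. youth, parents, and teachers" and goes on to say that these people "will be recruited from one school and one college at each site, resulting in a total sample of at least 30 participants".

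Study setting (2.1) supplies the missing multiplier: "Six sites will be included in the study". The section on feasibility assessment (2.6.4) confirms that the three groups are distinct recipients: "Each group will be offered the interventions designed specifically for them (youth, parents, and teachers".

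Nothing in the article restricts feasibility testing to a single site or gives another feasibility total. Table 1 describes the sample only as small.

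**The concern.** The sentence presents 30 as the result of the rule, yet the rule sets a minimum per group and applies it at every site. A total that follows from it must carry both the three groups and the six sites, and 30 cannot carry both.

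What is at stake is practical. A site team reading this text could reasonably conclude that it owes 5 people (30 shared over six sites), 15 (five per group) or 30 (five per group from each of two institutions). Feedback from this step goes to the expert panel, which recommends changes to the package before validation. The sites should therefore be working to one number, and a reader of the eventual report should be able to tell whether the planned size was reached.

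**Working it through.** **Inputs**
- Minimum per group: 5 (Sample size, feasibility paragraph).
- Groups: 3, namely youth, parents and teachers (same sentence; Feasibility assessment).
- Institutions per site: 2, one school and one college (same sentence).
- Sites: 6 (Study setting).
- Stated total: at least 30.

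**Trying to reproduce 30.** The total should be the minimum per group times every factor that the rule names.

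| Product | Result | Factor left out |
|---|---|---|
| 5 × 3 | 15 | sites and institutions |
| 5 × 3 × 2 | 30 | sites (one site's number) |
| 5 × 6 | 30 | groups (one group's number) |
| 5 × 2 × 6 | 60 | groups |
| 5 × 3 × 6 | 90 | none, if the five span school and college together |
| 5 × 3 × 2 × 6 | 180 | none, if five come from each institution |

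Thirty is reached in two ways, and each ignores something the sentence states.

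**What a total of 30 would mean**
- Per site: 30 / 6 = 5 people, against 15 (5 × 3) or 30 (5 × 3 × 2) under the rule.
- Per group per site: 30 / (3 × 6) = 30 / 18 = 1.67, against a minimum of 5.
- Relative to the rule: 30 / 90 = one third; 30 / 180 = one sixth.

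**How the same section counts elsewhere.** For the focus groups it plans "at least one FGD per stakeholder group per site, resulting in a minimum of 18 FGDs across six sites". That is 3 × 6 = 18, so a per-group, per-site rule is there multiplied by both groups and sites. The same convention applied to five people per group per site gives 90.

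**Whether the neighbouring total shows what was meant.** The validation total reads "With three participant groups, the total planned sample size will be a minimum of 354". With 59 per group, 59 × 3 = 177, and 354 is twice that. The figure equals 59 × 3 × 2 and also 59 × 6, just as 30 equals 5 × 3 × 2 and also 5 × 6. It is compatible with counting school and college while leaving out the sites, but it does not settle which factor was dropped from the feasibility total.

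**The case against.** The strongest reply is that both figures are floors. A team that recruited 90 or 180 would satisfy the minimum of five and also the total of at least 30, and a team following the operational rule would arrive at the larger number. This stands in part. The text does not establish that the feasibility sample will be too small, and a reader who infers that the step will run at 30 goes further than the wording allows. But the sentence offers 30 as the product of the rule, and a floor below the rule's own minimum permits a sample that breaks the rule.

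A second reply is that five per group might be meant for the whole study. That gives 15, not 30, and it sets aside the site wording that the same sentence contains.

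A third is that the step is formative: "Step 5 shall include testing and refining intervention on a small scale". It yields ratings and comments for an expert panel. This stands, and it limits the severity. It does not make the two halves of the sentence agree. Nor is this detail left to a fuller document, because both the rule and the total are stated here.

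Two further inferences are tempting, and the article does not support them. One is that 30 people would be spread too thinly to judge school and college versions of the package by role and site; the article describes no such versions and plans no such analysis. The other is that feasibility participants would be drawn again for validation. The sample-size text separates them from the development participants ("These participants will be different from the ones which were included in the sample for the development of the intervention package") and is silent about validation. Silence in a condensed article is not a contradiction, and nothing says that they will be redrawn.

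**Conclusion.** The point holds as an arithmetic inconsistency. Under the rule as written, with six sites and three groups, the minimum feasibility sample is 90 or 180. Which of the two depends on whether five applies per site or per institution, and the wording leaves that open. The stated 30 is one site's number or one group's number presented as the study total, and a sample of that size could not meet the stated minimum of five per group at each site.

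The conclusion assumes only that feasibility testing takes place at all six sites, which is what the recruitment wording and Study setting say. The article does not show which total the authors intended.

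Severity is low to moderate. The figure is a head count for formative feedback; no hypothesis test or power statement depends on it.

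**What to change.** State whether the minimum of five applies per group per site or per group per institution, and give the total with its product: 5 × 3 × 6 = 90, or 5 × 3 × 2 × 6 = 180. If 30 overall is what was planned, change the rule instead so that it no longer requires five per group at each site. One example would be five people per site over all groups, 5 × 6 = 30, with a statement of how the groups are shared among sites.

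The article reports that data collection has not begun, so this is a change of wording. If 90 or 180 was always intended and budgeted, it costs nothing more. If only 30 were budgeted, keeping the rule means recruiting 60 more people (90 − 30) or 150 more (180 − 30), while rewording the rule adds no recruitment.

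### Section 2.4: 59 per group in three groups makes 177, but the stated minimum total for validation is 354, and no multiplier explains the factor of two

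*Protocol article*

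**What the plan says.** Section 2.4 (Sample size) of the protocol article sets out the validation sample size in full, in four steps.

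- Design assumptions: an effect of 0.5, regarded as medium, tested at a "two-sided alpha of 0.05", with 95% power.
- Result: "This resulted in a requirement of 53 participants per group".
- Dropout: "Accounting for an anticipated dropout rate of approximately 10%, at least 59 participants per group will be recruited".
- Total: "With three participant groups, the total planned sample size will be a minimum of 354".

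The feasibility paragraph of the same section says what a group is: "A minimum of five participants per group (i.e. youth, parents, and teachers) will be recruited from one school and one college at each site". It then puts the feasibility total at 30 or more.

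Three other places bear on the count. Section 2.2 (Study design) has participants acting as their own controls. Section 2.7 (Statistical analysis plan) makes the pre-post comparisons inside each participant group and includes site as a random effect. Section 2.1 (Study setting) names six sites.

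**The concern.** The last step of the derivation does not follow from the ones before it. With at least 59 in each of three groups, the smallest total is 177, and the article gives 354. The ratio is exactly two, so rounding cannot explain it.

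This is the only enrolment target for the validation phase. A site team could stop at 177 because each group has reached 59, or go on to 354 because that is the stated total, and cite section 2.4 either way. Section 2.9 (Data management and monitoring) has a central monitor following recruitment, and that monitor has no single figure to follow.

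The possible explanations also differ in substance. If the doubling reflects school and college strata, 59 is the powered size within each stratum. If it is an allowance for clustering, cutting the total to 177 would remove it. If it is a slip, 354 recruits twice as many people, minors among them, as the stated calculation justifies.

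**Working it through.** **Inputs (section 2.4):** standardised effect d = 0.5; two-sided alpha 0.05; power 0.95; 53 per group; dropout about 10%; 59 per group recruited; three groups; total 354.

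**Step 1: the 53 per group.** The design is single-arm pre-post, so the paired formula applies.

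- Normal approximation: n = (z for 0.975 + z for 0.95)² / d² = (1.960 + 1.645)² / 0.25 = 51.98, so 52.
- Noncentral t: power is 0.9465 at n = 53 and 0.9502 at n = 54, so 54.

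The stated 53 lies between the two and is accepted. A two-sample comparison would need 104 (normal) or 105 (t) per arm, so 53 is not a two-arm figure.

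**Step 2: the 59 per group.** 53 / (1 − 0.10) = 58.9, so 59. This reproduces.

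**Step 3: the total.** 59 x 3 = 177, against 354 stated. 354 / 177 = 2 exactly. Equivalently, 354 = 59 x 6 = 118 x 3. This does not reproduce.

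**Step 4: can the article supply the missing factor?**

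| Candidate | Arithmetic | What the article says |
|---|---|---|
| Control arm | 59 x 3 x 2 = 354 | Excluded: own controls (2.2), within-group comparisons (2.7) |
| School and college counted separately | 59 x 3 x 2 = 354 | Stated for feasibility, not for validation |
| 59 at each of six sites | 59 x 6 = 354 | Conflicts with 59 being per participant group |
| 59 per group at each of six sites | 59 x 3 x 6 = 1,062 | Does not give 354 |
| Clustering allowance of 2 | 177 x 2 = 354 | Site random effect in 2.7, but no design effect in 2.4 |

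Every candidate that reaches 354 averages 354 / 3 = 118 per participant group. They differ in which unit the 59 describes, not in that average.

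**Step 5: consequence for power.** Paired, d = 0.5, two-sided alpha 0.05, no clustering:

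- Total 177: 59 recruited and 53 complete per group, power 0.947.
- Total 354: 118 recruited and 118 x 0.9 = 106 complete per group, power 0.999.

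**The case against.** The strongest reply is that both figures are floors. "at least 59 participants per group will be recruited" and a minimum of 354 are both met by enrolling 118 per group, so a team that reads the whole paragraph can comply with it. That is true, but it does not rescue the derivation: the article presents 354 as what three groups of 59 come to, and the minimum they come to is 177.

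The second reply is that the likely source stands in the same section. The feasibility total of 30 is 5 x 3 x 2, with one school and one college named, and 59 x 3 x 2 = 354 has the same pattern. Validation also recruits from schools and colleges (section 2.5). This makes an omitted phrase plausible and is a good reason not to presume that 354 is the error. It remains an inference. The feasibility sentence is also an imperfect precedent: it recruits at each site, yet its total contains no factor for the six sites.

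The third reply is that little statistical harm follows. Ignoring clustering, either total delivers essentially the stated 95%, and sections 4.1 and 4.3 say that this phase is not meant to establish causal effectiveness. That stands, and it limits the point to an unclear target.

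A reader might go further and infer that the target is known to be wrong by a factor of two, or that the validation phase is underpowered. The article supports neither. It does not show which number is wrong, and 53 completers per group already give about the intended power under the article's own assumptions.

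**Conclusion.** The validation total is wrong as written. The article's own group size and number of groups give 177, it states 354, and nothing in it accounts for the factor of two. The fault lies in the last step alone, since 53 and 59 both reproduce.

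The consequence is an enrolment target that can be read as 177 or 354. It is not a loss of the stated power. The power figures assume a paired comparison within each participant group, a standardised effect of 0.5, 10% dropout and no correlation within sites. The arithmetic contradiction rests on none of these assumptions.

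**What to change.** Give one reconciled calculation in section 2.4 and say what a group is for the validation phase. There are three consistent ways to write it:

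- Correct the total: 59 per group x 3 groups = 177.
- Keep 354 with the multiplier stated, for example 59 per group per institution type (59 x 3 x 2), and say that the 95% power applies within each stratum.
- Keep 354 as 118 per group (about 106 evaluable), give the reason for the doubling, and restate the power for that unit.

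The sponsor must choose, because the article does not show which was meant. If the doubling was an allowance for clustering, the assumed design effect should be stated with it.

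The text change is a few sentences, and sections 3 and 4.4 confirm that data collection has not begun. Whether the number recruited changes depends on which total the sites are now working to, which the article does not say.
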